## Abstract

**Background:**

Dysphagia, particularly sarcopenic dysphagia, is frequent in frail older patients. Sarcopenic dysphagia is a swallowing disorder caused by sarcopenia, corresponding to a loss of muscle mass and strength. It frequently leads to inhalation and to the decrease of food intake, leading the patient to enter a vicious circle of chronic malnutrition and frailty. The awareness of the major health impacts of sarcopenic dysphagia is recent, explaining a low rate of screening in the population at risk. In this context, methods of prevention, evaluation and intervention of sarcopenic dysphagia adapted to the most at-risk population are necessary.

**Methods:**

The DYSPHAGING (dysphagia & aging) pilot study is a prospective, multicentre, non-comparative study aiming to estimate the feasibility of an intervention on allied health professionals using the DYSPHAGING educational sheet designed to implement a two-step procedure ‘screen–prevent’ to mitigate swallowing disorders related to sarcopenic dysphagia. After obtaining oral consent, patients are screened using Eating Assessment Tool-10 Score. In case of a score≥2, procedures including positional manoeuvres during mealtimes, food and texture adaptation should be implemented. The primary endpoint of the study is the feasibility of this two-step procedure (screening–prevention measures) in the first 3 days after patient’s consent.

The study will include 102 patients, with an expected 10% rate of non-analysable patients. Participants will be recruited from acute geriatric wards, rehabilitation centres and long-term care units, with the hypothesis to reach a feasibility rate of 50% and reject a rate lower than 35%.

**Ethics and dissemination:**

The study protocol was approved according to French legislation (CPP Ile-de-France VII) on 15 February 2023. The results of the primary and secondary objectives will be published in peer-reviewed journals.

**Trial registration number:**

NCT05734586.

STRENGTHS AND LIMITATIONS OF THIS STUDYThe DYSPHAGING study is a pilot study focusing on geriatric patients in different care sectors.This study is based on a screening questionnaire recognised and used for the evaluation and follow-up of patients who benefit from rehabilitation and preventive measures of swallowing disorders complications.The DYSPHAGING study is a prospective pilot study that aims to estimate the feasibility of this intervention.Particular attention will be paid to the satisfaction of the nursing teams involved in the implementation of the questionnaire.

## Introduction

### Background and rationale

Sarcopenic dysphagia^1^ is a swallowing disorder (or oropharyngeal dysphagia (OD)) resulting from the expression of sarcopenia, characterised by the loss of muscle mass and strength due to age and chronic diseases, in the oropharyngeal tract. This condition gives rise to critical complications related to inhalation risks^2 3^ and exacerbates chronic undernutrition,^4^ creating a detrimental cycle. Although recent awareness of the high prevalence of sarcopenic dysphagia and its severe consequences among older individuals with disabilities and hospitalised patients has grown, the screening within the affected population remains low and challenging, leading to suboptimal care.^5^ In response, there is a pressing need for tailored prevention, assessment and intervention methods specifically designed for this vulnerable demographic.

To address this issue, the European Society for Swallowing Disorders and the European Union Geriatric Medicine Society have jointly developed a Dysphagia Working Group and published a white paper considering OD as a geriatric syndrome.^1^ This position paper advocated for increased awareness of swallowing disorders, utilisation of screening scores, preventive measures, standardised diagnostics and implementation of targeted interventions.

In adherence to these recommendations, we have collaboratively developed a pedagogical tool, entitled DYSPHAGING form, within our multidisciplinary unit, following a comprehensive four-step approach: (1) screening, (2) protection, (3) diagnosis confirmation and (4) rehabilitation. The form was designed to allow, in routine care, a rapid screening and protection procedure. Using standardised questionnaires and a simple, schematic iconography, it is expected to be handled in routine by nurses, care assistants and even caregivers. As a first step, the DYSPHAGING pilot study was designed to evaluate the feasibility of this screening and protection in diverse geriatric wards (acute care, rehabilitation and long-term care units).

## Methods and analysis

### Objectives

#### Primary objective

The primary objective of DYSPHAGING pilot study is to assess the feasibility of implementing steps 1 and 2 of the DYSPHAGING form in hospital care units within 3 days after the patient’s inclusion in the protocol.

#### Secondary objectives

Secondary objectives include: measurement of the percentage of eligible patients who refuse to participate in the study, characterisation of the target population (demographic and geriatric characteristics), quantification of non-implementation of protocol steps and reasons, description of factors associated with the risk of sarcopenic dysphagia, description of care team characteristics, satisfaction of the involved allied health professionals with the programme and difficulties encountered for its implementation.

### Trial design

DYSPHAGING pilot study is a prospective, non-comparative multicentre study conducted in three different geriatric departments and two different hospitals at the university hospital of Lyon (Hospices Civils de Lyon).

#### Study sites and participants

The study population will include older patient identified either during their admission (in acute care and rehabilitation units) or during systematic assessments in long-term care units.

Inclusion criteria are: age≥70 years, patient affiliated to a health system, informed of the study (information notice given) and having verbally indicated his/her non-objection to inclusion in the study.

Exclusion criteria are: patient either unable to be fed orally or with an active pathology responsible for acute swallowing disorders (<3 months): neurodegenerative pathology with predominant motor impairment such as Charcot disease, stroke, ear nose and throat pathology, patient under court protection, with progressive somatic or psychiatric pathologies that would impair his/her ability to perform study assessments, or for whom data collection is not possible.

Premature study exit criteria are: refusal to continue the study, transfer to another department within 3 days of screening, death. Data already collected will be kept and analysed.

### Intervention

The DYSPHAGING form was designed as a simple, clear, schematic and pedagogic recto–verso form to be easily handle in routine care (figure 1). The recto face contains the rapid Eating Assessment Tool (EAT-10),^6 7^ proposed by the Dysphagia Working Group as one of the most promising screening tools, as it is a self-reported questionnaire, shown to be internally consistent, reproducible and valid.^1^ A cut-off score of ≥2 was chosen, as Rofes *et al* demonstrated that it offers 89% sensitivity and 82% specificity for OD.^8^ The verso face contains three protection fields: postural manoeuvres, dietary and health rules and adaptation of food textures according to the standardised tool developed by the International Dysphagia Diet Standardization Initiative.^9^ The design of the form was developed multidisciplinary with dieticians and a particular attention was paid to the clarity and the understandability of the different schemas.

**Figure 1 F1:**
[figure not shown]
The DYSPHAGING (dysphagia & aging) form ((A) recto form and (B) verso form).

Following the transmission of an information notice and obtaining an oral consent from patients (and their legal guardian for patients under guardianship) by either a physician or a paramedical professional under his/her responsibility, the intervention involves the integration of patients into a structured screening and care process for sarcopenic dysphagia. The study aims to evaluate the ability of local caregivers, including nursing assistants and nurses in geriatric wards, to adhere to current screening recommendations and implement preventive measures in a routine and standardised manner. Additionally, patient characteristics will be collected at each site through a clinical research assistant (CRA) based on comprehensive medical records. The characteristics of the healthcare team and their satisfaction with the DYSPHAGING form will be assessed during this designated visit.

The intervention process consists of two steps: step 1: recto face of the DYSPHAGING form, consisting of the EAT-10 swallowing disorder screening questionnaire; in case of a score<2, the patient is considered fit for routine care without any additional protection measures; in case of a score≥2, the step 2 should be engaged within 3 days by the healthcare team to implement upper airway protection measures within the three protection fields (verso face of the DYSPHAGING form).

Patient characteristics will be collected at each site by a CRA based on comprehensive medical records. During this designated visit, the characteristics of the healthcare team and their satisfaction with the DYSPHAGING educational sheet will be assessed.

### Outcomes and measurements

*The primary outcome* of the study is the proportion of patients who fully complete steps 1 and 2 of the protocol. The endpoint is validated if either:

Step 1 is completed, and an EAT-10 Score<2.Step 1 is completed with an EAT-10 Score≥2 and step 2 is completed within 3 days following step 1.

*Secondary outcomes of the study* include:

The percentage of eligible patients who refuse to participate in the study.Patient characteristics, such as age, gender, comorbidities, functionality and comedications. Comorbidities will be assessed with the Cumulative Illness Rating Scale—Geriatric; functionality according to the activity of daily living (ADL)^10^ and instrumental ADL^11^ scores; comedications will be described according to the galenic form and drug class prescribed.Description of the factors associated with the risk of sarcopenic dysphagia (malnutrition, defined as either a weight loss >5% in the last 6 months, or >10% beyond 6 months, or a body mass index<22 kg/m²,^12^ patient at risk of malnutrition according to the mininutritional assessment short form, neurocognitive disorders, active pulmonary infection, chronic obstructive pulmonary disease, nutritional risk situations).The rate of partial completion of the protocol.The composition and disciplines of the healthcare team, the level of satisfaction and the difficulties encountered by the involved allied health professionals. A structured questionnaire was specifically designed to evaluate both dimensions (online supplemental document 1). Satisfaction will be explored using Likert scale questionnaires, counting 30 points concerning the initial presentation of the study to the healthcare team, 30 points concerning the feasibility to implement the protection interventions, 30 points concerning difficulties encountered during the study and 2 open questions concerning any missing pieces of information or suggestion to improve the study.

10.1136/bmjopen-2023-081333.supp1Supplementary data

### Trial conduct

The conduct of the study is represented in figure 2 and table 1.

Implementation: training by the principal investigator of the nursing teams at the investigation sites in the materials used in stages 1 and 2 of the DYSPHAGING protocol (EAT-10, checklist of measures to prevent swallowing disorders).Inclusion and screening:

**Figure 2 F2:**
[figure not shown]
Design of the DYSPHAGING pilot study. EAT, Eating Assessment Tool.

**Table 1 T1:** DYSPHAGING (dysphagia & aging) pilot study: flow diagram

Visits	V1	V2	End of the implementation of the measures
Time of evaluation	Inclusion	End of inclusion	End of the study
Patient			
Information notice	X		
Collection of non-opposition	X		
Inclusion and exclusion criteria	X		
Population demographics*	X		
Nutritional risk factors†	X		
Functional independence (ADL, IADL)	X		
Sarcopenic dysphagia risk factors‡	X		
Sarcopenic dysphagia screening (EAT-10)	X		
Airway protection measures§		X	
Care team			
Characteristics of the healthcare staff			X
Satisfaction questionnaire: Likert scale			X

*Population demographics are age, gender, comorbidities (Cumulative Illness Rating Scale—Geriatric) and comedications.

†Nutritional risk factors are assessed by the Mini Nutritional Assessment.

‡Risk factors for sarcopenic dysphagia include undernutrition, neurocognitive impairment, overt lung infections and chronic obstructive pulmonary disease.

§Upper airway protection recommendations are validated by the following three methods: postural manoeuvres, hygienic–dietary rules, textures within 3 days.

ADL, activity of daily living; EAT-10, Eating Assessment Tool; IADL, instrumental activity of daily living.

Inclusion: information to the patient is provided by either the physician or a paramedical professional under his/her responsibility, collection of non-objection and verification of inclusion and non-inclusion criteria, collection of patient characteristics and clinical data.On the same day as inclusion, performance of step 1 ‘screening’: dispensing of the 10-item EAT-10 screening questionnaire by a paramedical professional.If EAT-10 Score<2: end of patient participation.Completion of step 2 if EAT-10 Score≥2: implementation (within 3 days of screening) by the healthcare team of upper airway protection measures appropriate to each patient.

Completion of the following checklist:

Postural manoeuvres (sitting eating, chin down, ±head turned towards the paralysed limb, ±double swallow, ±Mendelsohn manoeuvre, ±forced swallow, ±(super)supraglottic swallow).Hygienic and dietary rules (eliminate risky foods, adapt fluids, take time, drink between sips, avoid distraction).Food textures (liquid, very slightly thick, slightly thick, moderately smooth/mixed smooth, mixed/pured, ground, swallowing specific soft, normal).Collection of the satisfaction and difficulties encountered by the involved allied health professionals with the programme (online supplemental table 1).

10.1136/bmjopen-2023-081333.supp2Supplementary data

Strategies for achieving adequate participant enrolment will regularly be implemented using formal (newsletters, posters, meetings) and informal methods to reach target sample size.

### Sample size calculation

The programme will be considered feasible, at the patient level, if the proportion of patients for whom steps 1 and 2 are achievable is statistically higher than 35%, with an anticipated proportion of 50% (= alternative hypothesis). Under these hypotheses, and assuming 10% of patients that might be non-evaluable, the inclusion of 102 patients will be necessary to achieve 90% power to show that the programme is feasible (one-sided alpha risk of 5%). The included patients will be analysed according to the intention-to-treat principle.

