### Descriptive analyses

A flow diagram will describe the data available for the patient population at baseline and during each follow-up visit. Eligibility criteria for treated patients will be verified, as well as follow-up and end of study visits. Reasons for premature end of study will be provided. Characteristics of the study population, numbers and proportions of missing values will be reported. Patient characteristics will be described using mean and SD or median and IQR for quantitative variables, and frequencies and distribution for categorical variables. A comparison of baseline characteristics between patients with complete follow-up and those with attrition will be performed. Analyses will be performed on the available data, without imputation for missing data.

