#### Primary analysis

The proportion of patients for whom steps 1 and 2 of the DYSPHAGING form in performed in the 3 days of inclusion will be assessed along with its corresponding 95% CI. Patients for whom information on the completion of steps 1 and 2 is not available will be considered as not having completed these steps.

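### The 102 patients allow for 10% being removed, but the primary analysis keeps patients without completion data as failures; if the 50% is a rate among evaluable patients, power is about 61%, not 90%

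*Protocol article*

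**What the plan says.** Under Sample size calculation, the criterion for declaring feasibility is that "the proportion of patients for whom steps 1 and 2 are achievable is statistically higher than 35" per cent. The hypothesised value is given next to it: "with an anticipated proportion of 50% (= alternative hypothesis". The test has a "one-sided alpha risk of 5" per cent. The same section gives the size: "assuming 10% of patients that might be non-evaluable, the inclusion of 102 patients will be necessary to achieve 90% power". The Methods paragraph of the abstract describes the allowance in slightly different terms: "The study will include 102 patients, with an expected 10% rate of non-analysable patients".

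Two statements fix who is analysed. The sample size section ends: "The included patients will be analysed according to the intention-to-treat principle". The Primary analysis section adds: "Patients for whom information on the completion of steps 1 and 2 is not available will be considered as not having completed these steps". The section on study sites and participants also says that data already collected from patients who leave early (refusal, transfer, death) are retained in the analysis.

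A further sentence, under Descriptive analyses, reads: "Analyses will be performed on the available data, without imputation for missing data".

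**The concern.** Dividing a sample size by 0.9 protects power only if the missing 10% drop out of both numerator and denominator. The patients who remain then still have the planned success rate, and there are still enough of them. When the same patients stay in the denominator and count as failures, the sample does not shrink. The success proportion does, and with it the distance from the 35% null. Adding patients by the factor 1/0.9 does not make up for that.

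The feasibility verdict rests on this one test. If power is well below the stated 90%, a programme that performs as hoped could be declared not shown feasible far more often than the 10% that readers will infer. The article's discussion says that the pilot should inform a larger study, so a false negative would carry forward.

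**Working it through.** **Inputs.** Null 35%, alternative 50%, one-sided alpha 5%, power 90%, 10% non-evaluable, 102 inclusions (all from Sample size calculation). Missing completion information counts as not completed (Primary analysis).

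**Step 1: reproduce 102.** One-sample proportion, normal approximation with null and alternative variances:

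n = [(1.645 × √(0.35 × 0.65) + 1.2816 × √(0.5 × 0.5)) / 0.15]²
= [(0.7845 + 0.6408) / 0.15]² = 9.502² = 90.3, rounded up to 91.

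91 / 0.9 = 101.1, rounded up to 102. This matches the plan. The 90% power therefore belongs to 91 evaluable patients with a 50% success rate among them (90.2% by the normal approximation, 89.6% exact).

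**Step 2: apply the primary analysis rule.** Suppose that 10% of included patients lack completion information and 50% of the others succeed. The expected proportion among all included patients is 0.90 × 0.50 + 0.10 × 0 = 0.45. The difference from the null falls from 15 to 10 percentage points.

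**Step 3: power with 102 patients.** Let X be the number of completers.

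| Success rule | True one-sided alpha, P(X ≥ c) at 35% | Power at 45% | Power at 50% |
|---|---|---|---|
| Exact test, X ≥ 45 | 3.5% | 60.8% | 90.1% |
| Normal-approximation rule, X ≥ 44 | 5.4% | 68.3% | 93.1% |

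The second rule exceeds the planned 5%, so the first is the proper reference. The continuous normal formula at 45% gives 67.5%.

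**Step 4: sensitivity to the share counted as failures.** With 5%, the tested proportion is 0.95 × 0.50 = 47.5% and exact power (X ≥ 45) is 78%. With 8%, it is 0.92 × 0.50 = 46% and exact power is 68%.

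**Step 5: the other readings.**
- The 50% already covers all included patients, with missing data as failures: exact power is 90.1% (last column, first row). The 10% then enters nowhere.
- The 10% are truly excluded from the analysis: with 91 or 92 analysed at 50%, exact power is 89.6% (X ≥ 40) or 87.4% (X ≥ 41). This agrees with the inflation, but it needs an exclusion that the primary analysis does not provide for.

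**The case against.** The strongest reply is that the loss of power is conditional. The protocol never says that the 50% is a rate among evaluable patients. Read literally, it is a proportion of patients, in a section that goes on to specify intention to treat. On that reading the stated power holds. Nor does the article equate its non-evaluable or non-analysable patients with those whose completion information is unavailable. They could be patients left out for another reason, such as being found ineligible, and would then not be failures. Both points stand. A reader might infer that the trial's actual power is 61% to 68%. The documents do not support that as a flat statement, because it is the result under one reading.

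The 0.9 × 50% model is also simpler than the trial. Screening takes place on the day of inclusion, and a score below 2 completes the endpoint at once, so such patients cannot be lost through later transfer or death. An early exit is therefore not automatically a failure. This stands too, and it is a reason to show the 5% case beside the 10% case.

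A reader might further take the available-data sentence as contradicting the failure rule. It does not: it appears under Descriptive analyses, and the Primary analysis section gives the specific rule for this endpoint, which governs.

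What the objection does not remove is the mismatch. If the 50% covers all included patients, the allowance is redundant, although the text makes it part of the reason why 102 are needed. If the 50% covers evaluable patients, the power is overstated under the failure rule.

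**Conclusion.** The point holds as an inconsistency between the sample size justification and the primary analysis. It is not an arithmetical error, since 102 reproduces exactly.

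The size of the problem depends on two assumptions: that 50% is the rate among evaluable patients, which the division by 0.9 implies but does not prove, and that the non-evaluable patients are those counted as failures. With both, a programme performing as hoped would miss the feasibility criterion in about 39% of trials by the exact test (100 − 60.8) or about 32% by the normal-approximation rule (100 − 68.3), against the 10% implied. Without the first, power is as stated and only the justification is wrong. Under the published failure rule, there is no reading in which the 90% and the 10% allowance are both right.

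The failure rule is conservative and does not raise the risk of a false claim of feasibility. The conflict lies between statements that the article itself fixes, so it is not a detail left for the later analysis plan.

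**What to change.** Keep 102 patients and keep counting missing completion information as not completed. Then choose one statement, according to what the 50% was meant to describe:

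- (a) The anticipated 50% applies to all included patients, with missing data counted as failures. Delete the 10% allowance from the sample size section and the abstract, and state exact power of 90.1% with success at 45 or more of 102.
- (b) The anticipated 50% applies to evaluable patients. Restate the power as about 61% (exact, same success threshold) at 10% non-evaluable.

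In either case, report the proportion among evaluable patients as a sensitivity analysis, and say who counts as non-evaluable for that purpose. The available-data sentence needs no change for the primary endpoint.

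The cost is wording and, under (b), a less favourable stated power. No extra patients are needed. Enrolment is under way, so the choice should be recorded before the database is frozen, when the analysis plan is due.
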